### Sample size calculation

This is a feasibility trial therefore we have not undertaken a formal sample size calculation. A sample size of 40 participants in each group will be adequate to provide estimates of direction and magnitude of any effects, and to provide an estimation of variability for later sample size calculation. Previous literature shows that a sample size of between 30 and 36 per arm is adequate for a feasibility trial [55]. We based our sample size on that information, on our knowledge of likely participants to the art program, and on information from our previous experience of likely drop-out rates from stroke rehabilitation trials.

### Fidelity

The project processes will be facilitated by the use of clear written information: guidance to rehabilitation staff on the stroke units about identifying eligible patients, clear protocols for the artists, use of individual patient case reports to log each stage of the project process and training for all researchers in outcome measures. The project researchers will be in regular contact with the stroke units to provide support and to deal with any problems.

### Withdrawal from study

There will be five points at which a participant may withdraw from the study - prior to completing baseline questionnaires, prior to commencement of the CEI, prior to completion of the CEI, after completion of the CEI but prior to completion of outcome measures and prior to completing the three-month follow-up assessment.

We do not anticipate any harms occurring as a result of participation in this study, however, we remain alert to that possibility. Withdrawal will occur if the participant requests it, if the participant is unable to participate in any aspect of the study or if there is any indication that participation is causing harm of any kind.

### Data confidentiality and management

All records will be securely stored in locked cabinets in areas with restricted access. All administrative and data records will be identified by a coded identification number to maintain participant confidentiality, and these will be kept separately from records containing names and other personal identifiers. All databases will be secured with password-protected access systems. TCTU will be responsible for data management, data quality assurance, backup, business recovery and statistical analysis. A formal data monitoring committee was not required because this is a feasibility trial.

### Statistical analysis

The Montreal Cognitive Assessment and the National Institutes of Health Stroke Scale will provide screening data and indicate baseline status. Other baseline characteristics to be collected are: age, sex, handedness, ischemic or hemorrhagic stroke, side of hemiplegia, Barthel Index, Aphasia Severity Rating Scale [56] and use or not of psychotropic medication. Preference for randomization to the intervention group (participating in art) or the control group (viewing art) will be assessed after randomization.

Data analysis will be undertaken blind to group allocation. The primary analysis will be based on the intention-to-treat principle. Proportions of missing data will be examined to inform decision-making about selection of outcome measures for the definitive trial. Transformations of the outcome variables will be used where necessary if these are not normally distributed. All analyses will incorporate the stratification factors.

Data will indicate, with confidence intervals, the proportion of patients choosing or refusing participation in the CEI and will allow calculation of recruitment rates for a future definitive trial. Data about the proportion of study dropouts will also provide information that will inform a definitive trial. Summary data from measures will indicate potential variability, magnitude and direction of difference between groups at the end of intervention and at three-month follow-up.

To examine the effects of the intervention, a repeated measures analysis using mixed models will be conducted for outcomes, although these will not involve definitive hypotheses testing. Adjustment for baseline factors and mediating variables will be undertaken by adding these as covariates to give an idea of which factors are important in determining outcome. This will indicate where the intervention effects are likely to occur and will generate power calculations for a future definitive RCT. The measure with greatest difference as well as most relevance in the feasibility study will be selected as primary outcome measure, whilst taking into account proportions of missing data. Missing data will be examined for randomness, and if appropriate, multiple imputations will be conducted to replace missing values. Intention-to-treat analysis based on outcome evaluation of cases as randomized will be conducted to examine any important differences in findings. Reporting of results will adhere to Consolidated Standards of Reporting Trials criteria for the reporting of randomized controlled trials [57].

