Undertaking an RCT to evaluate the effects of a CEI on psychosocial outcomes is, however, challenging and a number of uncertainties need to be clarified before proceeding to a full-scale phase III trial. Firstly, the feasibility of undertaking a trial of a non-traditional intervention in a rehabilitation setting needs to be established. Art is an intervention in which preference for participation may strongly influence participant recruitment and attrition and therefore, before proceeding to a full trial, it is vital to identify the role of preference in recruitment and trial participation. Secondly, components of the intervention and their mechanisms of action need to be made explicit. Thirdly, the precise outcomes likely to be influenced by the intervention and corresponding appropriate measures that can be completed by stroke survivors need to be identified.

Selection of appropriate outcome measures is a particular challenge to researchers designing studies to measure the intervention effects of CEI. This is challenging given that the exact mechanisms by which art may influence psychosocial outcomes have not been fully established for stroke survivors. The present trial design is derived from an initial qualitative study that aimed to identify for the purposes of the trial, the components, mechanisms of action and perceived effects of an existing visual art CEI for stroke survivors receiving in-patient rehabilitation. Findings from the qualitative phase were used to design the feasibility trial intervention protocol and identify the outcomes to be evaluated to test the effects of the intervention. The purpose of the present study is to test trial processes to identify feasibility issues in running a CEI, to identify the primary outcome measure and to provide an assessment of effect size for power calculations for a full-scale Phase III trial. The purpose of this manuscript is to describe the trial design and protocol for a feasibility trial.

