### Study aims

The aim of this study is to examine the feasibility of conducting an RCT to assess the potential effectiveness of a CEI to improve psychosocial health outcomes in patients receiving in-patient rehabilitation after stroke. To inform the development of a future Phase III trial, we will examine rates of recruitment of patients within in-patient rehabilitation wards to the trial. We will also examine the impact of preference for art on recruitment, retention and outcomes, and explore the acceptability and usefulness of the intervention from the perspective of patients and health professionals. A final aim is to estimate completion rates and effect sizes for relevant patient outcomes to inform the selection of a primary outcome measure and sample size calculations for a full-scale trial.

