### Recruitment

Nursing and rehabilitation staff will identify potentially eligible patients within one week of admission to either of the stroke unit research venues, or when patients are medically stable and able to participate. The nursing and rehabilitation staff will provide and explain information leaflets to patients about the study, with an invitation to participate. One of two study researchers will approach patients who indicate interest in participating. The study will be fully explained, questions will be answered and initial screening for participation based on communication and comprehension will be will be conducted. Written informed consent for participation will be obtained. Ability to provide informed consent will be guided but not limited by scores on the following measures:

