### Randomization

Randomization to a control group or an intervention group will be conducted using a remote web-based concealed computer-generated randomization system organized through Tayside Clinical Trials Unit (TCTU). To minimize the likelihood of imbalance between groups, for each site we will stratify according to age (≤60 years, 61 to 80 years, and ≥81 years), gender and disability. Disability will be assessed using routinely collected data from the Barthel Index [35], a scale measuring independence in activities of daily living. The maximum score is 100, indicating independence. Participants will be stratified according to scores that indicate likelihood of independence in activities of daily living (0 to 40, 45 to 55, 60 to 100) [36]. Tayside Clinical Trials Unit (TCTU) will set up a password-accessed online randomization system that will be accessed only by research staff. After baseline assessment, the study researcher will enter stratification details. The system will determine random allocation after which the artists will be informed.

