### Control group

Control participants will receive the same usual rehabilitation as the intervention group. Reflecting usual practice within the units, art made by previous participants will be available for viewing. After baseline assessment and randomization, the control group will receive from the study researcher a portfolio of work produced by previous participants of the Tayside CEI, with details of the community programs that people with stroke can attend after hospital discharge. Participants will be given the portfolio and invited to view it during their rehabilitation stay. Prior to outcome assessment, the study researcher will visit participants again to answer questions and to discuss options for community programs, if the person is interested.

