### Trial procedures

Once participants meeting inclusion criteria have provided informed consent to participate, one of two study researchers will collect data indicating participant characteristics and will undertake baseline assessments. Stratification factors will be entered into the concealed online randomization system by the study researchers, who will inform the artists of group allocation. Participants in the intervention group will be invited to attend one individual and one group intervention session per week with the artist, for up to a maximum of eight sessions. The art portfolios will be delivered to participants allocated to the control group after baseline assessment.

A third researcher, blinded to group allocation and trained to administer outcome measures, will undertake outcome assessment with participants in the intervention group after eight art sessions, or at hospital discharge, if that occurs beforehand. The blinded researcher will undertake outcome measures with the control group at four weeks, or at discharge if that occurs prior to four weeks. Participants will be instructed not to reveal their group allocation to this researcher, but any episodes of un-blinding will be recorded. Three months after outcome assessment, the researcher will contact participants to arrange a follow-up assessment, which will be conducted in hospital or at the participants’ home, depending on discharge status. Nine participants from the intervention group and three from the control group, purposefully selected to reflect age, disability and gender, will also be invited to participate in audio-recorded in-depth interviews after follow-up assessment to evaluate their experiences of participation in the CEI, and the trial.

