Confidence that personal rehabilitation goals and art-specific goals could be achieved was generated through the opportunities for skill acquisition that art provided. Confidence was inferred by the qualitative study as a route by which art participation improved recovery, self-esteem and mood. We therefore included a measure of general self-efficacy [49–52] and one that examines self-efficacy for art [46], to evaluate whether art improves self-efficacy and influences more distal outcomes, such as stroke recovery. Perceptions of difficulty can also influence self-efficacy therefore a single-item measure to assess difficulty has been included, as suggested by Francis *et al*. [52].

Hope appears to predict better rehabilitation outcomes. Hope occurs when a person perceives routes to achieving goals and has motivation to access those routes [53, 47]. It has been hypothesized that in rehabilitation hope buffers negative emotions because the individual believes that goals can be achieved despite obstacles [48, 54]. Hope was another concept that our qualitative interviews suggested was developed through art participation. We therefore included the Hope Trait Scale [47] as a secondary outcome. The scale measures hope agency thinking, which represents a patient’s wilful sense of determination to meet goals, and pathway, which reflects a patient’s perceived availability of ways to attain a goal.

This is a pilot trial, therefore as well as clinical and psychological outcomes, we are also collecting data on other outcomes that relate to the feasibility of conducting a definitive trial. We will collect data and evaluate trial recruitment rates, the proportion of participants who prefer to be randomized to art and retention and dropout rates. We will examine the variability of scores on outcome measures and completion rates and ease of use of the chosen measuring instruments at each assessment point. We will also undertake comparison between the measures to determine which are more appropriate for use in a definitive trial. Finally, we will evaluate with participants and staff, the acceptability and feasibility of undertaking the trial in rehabilitation settings.

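### Preference for art is asked only after randomisation, and nothing says allocation is withheld until then, so its role in retention, outcome and recruitment cannot be cleanly estimated

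*Protocol article*

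**What the plan says.** The Statistical analysis section lists the baseline characteristics and then, in a separate sentence, fixes the timing of one further item: "Preference for randomization to the intervention group (participating in art) or the control group (viewing art) will be assessed after randomization".

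Preference is not incidental to this trial. The Background says that before a full trial "it is vital to identify the role of preference in recruitment and trial participation". Study aims states: "We will also examine the impact of preference for art on recruitment, retention and outcomes". The Outcome measures section lists among the feasibility data "the proportion of participants who prefer to be randomized to art and retention and dropout rates".

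On who knows the allocation, Trial procedures blinds the third researcher, who assesses outcomes, and adds: "Participants will be instructed not to reveal their group allocation to this researcher, but any episodes of un-blinding will be recorded". The Control group section says: "After baseline assessment and randomization, the control group will receive from the study researcher a portfolio of work produced by previous participants of the Tayside" art program. Intervention participants are invited to sessions with an artist.

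On the order of events, the Randomization section says: "After baseline assessment, the study researcher will enter stratification details". A data collection point before allocation therefore already exists.

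**The concern.** A preference stated after allocation, by someone who may know the allocation, is not purely a prior preference. It can also carry satisfaction, disappointment or rationalisation. Three uses of the variable are then exposed.

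- **Retention and outcome.** Comparing dropout or outcome by stated preference conditions on something the allocation may have changed. An association could appear where there is none, or a real one could be diluted.
- **Recruitment.** Everyone who is asked has already been recruited, so the variable offers no contrast with people who were not.
- **Planning.** The proportion preferring art could mix prior preference with reaction to allocation.

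At stake is a named aim, on a question that the authors regard as needing an answer before a definitive trial.

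**Working it through.** **No stated figure to reproduce.** The article makes no formal sample size calculation and gives no figure for preference. The only number from it used here is 40 per arm, 80 in total. Everything else below is an assumption made for illustration.

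**Step 1: order of events.** Consent comes first, then baseline assessment, entry of stratification details, allocation, and informing the artists. Portfolio delivery to controls also follows allocation. Preference is placed after allocation. No section says when the participant is told the arm, or whether the preference question comes before or after that.

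**Step 2: recruitment.** To estimate how preference affects recruitment, one needs preference in both recruited and non-recruited people. Among those asked after randomisation, all are recruited. The effect is not estimable from this variable, whatever the size of any shift in answers.

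**Step 3: proportion preferring art, symmetric shift.** Let p be the true proportion preferring art. Let s be the share of those allocated against their preference who report the arm they received.

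- Art arm: p + s(1 − p)
- Control arm: p − sp
- Gap between arms: s
- Pooled with equal arms: p − s(2p − 1)/2

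With p = 0.60 and s = 0.20:

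- Art arm: 0.60 + 0.20 × 0.40 = 0.68
- Control arm: 0.60 − 0.20 × 0.60 = 0.48
- Pooled: (0.68 + 0.48)/2 = 0.58, an error of 2 points
- 95% half-width at n = 80: 1.96 × √(0.60 × 0.40/80) = 0.107, about 11 points

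Over p = 0.5 to 0.8 and s = 0.1 to 0.3, the pooled error runs from 0 (p = 0.5) to 0.3 × 0.6/2 = 0.09. Only at that extreme corner does it reach the sampling half-width, which is 0.088 at p = 0.8.

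**Step 4: the opposite direction.** Suppose instead that the art arm does not shift, and that 20% of controls who truly prefer viewing say they wanted art. Controls then report 0.60 + 0.20 × 0.40 = 0.68 against 0.60 in the art arm. The gap is 8 points the other way, and the pooled figure is (0.60 + 0.68)/2 = 0.64. The sign of any artefact is therefore not established.

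**Step 5: outcome by preference.** Return to the model of Step 3, with switching unrelated to outcome. A true difference in outcome by preference is diluted by p/[p + s(1 − p)] = 0.60/0.68 = 0.88 in the art arm, and by (1 − p)/(1 − p + sp) = 0.40/0.52 = 0.77 in the control arm.

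**Step 6: retention by preference.** Take 100 controls, 60 truly preferring art, with an assumed 20% dropout whatever the preference. Suppose only future completers switch, with s = 0.20.

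- Dropouts: 12 report art, 8 report viewing.
- Completers: 48 × 0.80 = 38.4 report art; 32 + 9.6 = 41.6 report viewing.
- Apparent dropout: 12/50.4 = 23.8% among reported art, 8/49.6 = 16.1% among reported viewing.

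The true figure is 20% in both, so the association is entirely spurious.

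**The case against.** The strongest reply is that the article says after randomisation, not after disclosure. If the question were put once the system had allocated but before the participant was told, the threat to the retention and outcome analyses would largely disappear. This stands as a limit on certainty: a reader might infer that participants already know their arm when asked, but the document does not state it. It remains a strong inference, because participants do come to hold their allocation and no step for withholding it is described. The recruitment problem remains either way.

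A second reply is that other provisions cover preference. The Statistical analysis section plans a proportion of patients choosing or refusing the CEI, and the Qualitative phase explores preference in interviews. These help only indirectly. The first counts participation rather than preference. The second involves 12 purposively selected, already randomised participants after three-month follow-up. Neither gives a measure of preference free of allocation.

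A third reply is that no preference-by-arm model is specified, that preference is not named as a covariate in the mixed models, and that no definitive hypothesis tests are planned. That is correct, and it limits the harm to the preference aim. It does not rescue that aim.

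**Conclusion.** The point holds in a limited form. The plan fixes the preference question after randomisation in a trial whose participants are not blinded, with no stated safeguard on disclosure. Analyses of retention and outcome by preference would then rest on a post-randomisation variable, and the effect on recruitment cannot be estimated from it at all.

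Two stronger readings are not supported.

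- A reader might infer a spurious gap between arms of 10 to 30 points. That figure only returns the assumed s. Nothing in the document informs s, and Step 4 shows that the sign could reverse.
- A reader might infer that the planning figure for preference is badly wrong. Under the symmetric shift, the pooled figure in the worked example is 58% against 60%, well inside the sampling error. This modest size depends on the shift being symmetric and on equal arms.

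The randomised comparison between arms is unaffected, provided post-allocation preference is not entered as a covariate in the mixed models described under Statistical analysis.

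**What to change.** Record preference at the baseline assessment, after consent and before the researcher opens the randomisation system. Use only that value in any analysis by preference. This removes allocation-driven shift: the expected gap between arms becomes zero. Precision for the proportion at n = 80 is about 9 to 11 points for p between 0.5 and 0.8.

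The move to baseline does not by itself repair the recruitment part of the aim, because consenters have already been recruited. For that, ask the same question of eligible patients who decline and are willing to answer. Where that cannot be done, make no claim about the effect of preference on recruitment.

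The Trial status section reports recruitment as finished. If the data are already collected, state when the question was asked relative to disclosure, report preference by arm as a post-allocation response, and keep it out of the covariate models.

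The cost is one question moved to the baseline form and one line on the screening record. A small downside is that voicing a preference first may slightly heighten disappointment with allocation.

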**Methods/Design:**

This trial is a two arm, single-blind, randomized controlled feasibility trial within in-patient stroke rehabilitation. We will recruit 80 patients receiving stroke rehabilitation in two stroke units in a health board area of Scotland (40 patients in each arm). Intervention arm participants will receive a visual-arts based CEI facilitated by experienced artists. Artists will follow an intervention protocol with specific components that enable participants to set, achieve and review artistic goals. Participants will receive up to eight intervention sessions, four within a group and four one-to-one with the artist. Control group participants will receive usual care only.

Data collection will occur at baseline, post-intervention and three-month follow-up. Stroke-related health status is the primary outcome; mood, self-esteem, self-efficacy, perceived recovery control and hope are secondary outcomes. Semi-structured interviews will be conducted with purposively selected patients, artists and healthcare staff to elicit views and experiences of the intervention and feasibility and acceptability of trial processes. Recruitment rates, retention rates and patient preference for art participation will also be collected. Data will indicate, with confidence intervals, the proportion of patients choosing or refusing participation in the CEI and will allow calculation of recruitment rates for a future definitive trial. Summary data will indicate potential variability, magnitude and direction of difference between groups. Findings will inform sample size calculations for a definitive trial. Thematic analysis of qualitative data will be managed using the Framework Approach. Framework is an analytical approach for qualitative data, commonly used in policy and medical research.

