### Outcome measures

The proposed outcome measures were selected to reflect clinical and stroke-related outcomes likely to be affected by the intervention. The final selection of primary outcome for a definitive trial will be determined by the findings of this feasibility trial, but our exploratory work indicates that stroke-related health status measured by the Stroke Impact Scale, is likely to the primary outcome measure. The scale examines communication, participation in life roles, physical status and mood, which were key outcomes indicated by the qualitative work as important benefits of art participation. In addition, the Positive and Negative Affect Scale was selected to investigate positive emotions such as enthusiasm and alertness, which our qualitative work and other recent studies [26] indicate might be influenced by art participation. Similarly, the qualitative work demonstrated that stroke survivors perceive improved self-esteem through art participation, but more specifically from the final stage of the intervention, in which the artwork is displayed and viewed by others. We therefore included the Visual Analogue Self-Esteem Scale [45] as an outcome measure.

To examine underlying psychological constructs that appear to explain how art might influence improvements in the above outcomes, we have also included other secondary outcome measures. Participants in the qualitative study indicated these as important. Survivors suggested that recovery of upper limb function and communication occurred because art provided them with the opportunities to develop their own control of these aspects of stroke recovery in ways that other rehabilitation did not. The art itself provided ways in which survivors could use their upper limbs and try out activities for themselves. Interactions with the artists and within the group provided an environment in which survivors could practice and regain control over their communication. We have therefore included as an outcome the recovery locus of control [46], which indicates internal or external locus of control over recovery and will provide a measure of change in control as a result of art participation.

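### Mediating variables are to be added as covariates in the intervention-effect model, and no mediator-free estimate is reserved for the power calculation or the choice of primary outcome

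*Protocol article*

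**What the plan says.** The Statistical analysis section of the protocol article sets out the effect analysis: "To examine the effects of the intervention, a repeated measures analysis using mixed models will be conducted for outcomes". It adds that no definitive hypothesis tests are intended. It then states: "Adjustment for baseline factors and mediating variables will be undertaken by adding these as covariates", with the stated purpose of learning which factors matter for outcome. The next sentence reads: "This will indicate where the intervention effects are likely to occur and will generate power calculations for a future definitive RCT". The one after that gives the rule for the definitive trial's main endpoint: "The measure with greatest difference as well as most relevance in the feasibility study will be selected as primary outcome measure", with missing data also taken into account.

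The Outcome measures section shows what the mediating variables are likely to be. A group of secondary measures is included "To examine underlying psychological constructs that appear to explain how art might influence improvements in the above outcomes". Recovery locus of control "will provide a measure of change in control as a result of art participation". Self-efficacy is measured "to evaluate whether art improves self-efficacy and influences more distal outcomes, such as stroke recovery". Hope is included because the preparatory interviews suggested that it grows through taking part in art. On timing, the abstract says: "Data collection will occur at baseline, post-intervention and three-month follow-up".

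The Specific objectives section asks for the effect size of the intervention against usual care. The primary analysis follows intention to treat.

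**The concern.** Baseline factors and mediators are placed in one adjustment step, but they act differently. A baseline covariate cannot be affected by allocation. Adjusting for it leaves the treatment effect in place and usually sharpens it. A mediator is affected by allocation and lies between treatment and outcome. With it in the model, the treatment coefficient no longer includes the part of the effect that passes through it. Mediator and outcome may also share causes that randomisation does not balance once one conditions on the mediator, so the coefficient may not be a valid direct effect either.

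Two outputs of the feasibility trial are exposed. One is the effect size and SD carried into the definitive trial's sample size. The other is the choice of primary outcome by largest difference, where measures that respond through control, self-efficacy or hope would lose most.

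**Working it through.** **Figures in the plan.** The Sample size calculation section states 40 per group (2 × 40 = 80) with no formal calculation. It gives no alpha, power, effect size or SD, so there is no figure to reproduce, and the 80 is not disputed. All inputs below are assumptions.

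**Assumed inputs.** Two-sided alpha 0.05, 80% power, 1:1 allocation, one outcome time point. Within-arm SD is 1 for outcome and mediator. Total effect D = 0.5 (0.3 as an alternative). Mediated share s = 25%, 50% or 75%. Within-arm slope b of outcome on mediator is 0.3 to 0.6.

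**Formulas.**
- Linear model without mediator-outcome confounding: adjusted coefficient = D × (1 − s).
- Residual SD of the adjusted model = √(1 − b²): 0.954 at b = 0.3 and 0.800 at b = 0.6.
- n per arm = 2(1.960 + 0.8416)² × (SD/effect)² = 15.698 × (SD/effect)², rounded up.

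**Without the mediator, D = 0.5.** 15.698 / 0.25 = 62.8, so 63 per arm.

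**With the mediator, D = 0.5.**

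| Mediated share | Adjusted coefficient | n per arm, SD 1 | n per arm, residual SD (b = 0.6 to 0.3) |
|---|---|---|---|
| 25% | 0.375 | 112 | 72 to 102 |
| 50% | 0.250 | 252 | 161 to 229 |
| 75% | 0.125 | 1,005 | 643 to 915 |

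For example, at 50% with SD 1, 15.698 / 0.0625 = 251.2, so 252. With residual SD 0.8, 251.2 × 0.64 = 160.7, so 161. The smaller residual SD offsets only part of the loss.

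**With D = 0.3 and SD 1.** 175 per arm without the mediator; 311, 698 or 2,791 with it.

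**Simulation check** (400,000 records, D = 0.5, s = 50%, b = 0.5, correlation 0.6 between the baseline mediator and the within-arm part of the later mediator):

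| Model | Treatment coefficient | Residual SD |
|---|---|---|
| Unadjusted | 0.496 | 0.999 |
| Adjusted for baseline mediator value | 0.496 | 0.953 |
| Adjusted for post-randomisation mediator value | 0.247 | 0.865 |

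The baseline version keeps the effect and reduces the SD. The post-randomisation version halves the effect.

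**Mediator-outcome confounding.** Let an unmeasured cause load 0.4 on both mediator and outcome. With a the effect of art on the mediator and b the causal slope, the fitted mediator slope becomes b + 0.4 × 0.4 and the adjusted coefficient is total − a × (fitted slope). With a = 0.4, b = 0.5 and direct effect 0.10, the total is 0.10 + 0.4 × 0.5 = 0.30. The fitted slope is 0.66 and the adjusted coefficient 0.30 − 0.4 × 0.66 = 0.036, which is not the true direct effect of 0.10.

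**Choice of primary outcome.** Take one outcome with total effect 0.5, 75% mediated, and another with total effect 0.3, 25% mediated. Their adjusted coefficients are 0.125 and 0.225. The ranking by largest difference reverses.

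**The case against.** The strongest reply is that the mediator step is a side analysis. The sentence has an exploratory purpose, and adding covariates implies a base model that lacks them. In the power-calculation sentence, the opening word "This" may refer to the mixed-model work as a whole. The abstract and the Statistical analysis section also promise group summaries of magnitude, direction and variability, and the Sample size calculation section expects an estimate of variability for later planning. An unadjusted difference and SD will therefore exist. The protocol never says at which time point the mediators enter, and that detail could sit in an analysis plan that is not shown.

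Much of this stands. The timing is inferred, although mediators are listed apart from baseline factors and are described as changed by art, which baseline values cannot be. The link to the power calculation is the nearest reading of the text but not the only one. What does not stand is that the text already separates the two analyses. Nowhere does it reserve a mediator-free estimate for planning or for selecting the outcome.

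A reader might go further and infer that both inputs to the definitive sample size will be wrong. The documents do not establish that, because the planned summaries could be used instead. A reader might also infer that the estimate changes sign whenever the mechanism works. It does not: under the linear model without confounding, full mediation gives zero. A negative value in this kind of example needs a shared cause as well, as with no direct effect, a = 0.5, b = 0.4 and loadings of 0.4: 0.20 − 0.5 × 0.56 = −0.08.

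**Conclusion.** The concern holds as a fault in what the text fixes. Followed as written, the adjusted coefficient is not the effect against usual care, and nothing prevents it from feeding the power calculation and the outcome choice. If it did, and half of an assumed 0.5 SD effect were mediated, the definitive trial would be planned at 161 to 252 per arm instead of 63, about 2.6 to 4 times too large.

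That size rests on assumed effects, mediated shares and slopes, a linear model, a well-measured mediator and no confounding. Where these fail, removal of the mediated part may be incomplete and other bias may be added. If only baseline values were meant, there is no bias, but they are then not mediators. Severity is moderate: the trial is an exploratory feasibility study, and no definitive efficacy test depends on this step.

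**What to change.** In the Statistical analysis section, split the adjustment sentence in two.

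1. State that the effect and SD used for the power calculation, and the differences used to select the primary outcome, come from a model with arm, time, arm-by-time, baseline value of the outcome and the stratification factors. Other covariates measured before randomisation are acceptable, including baseline values of control, self-efficacy and hope.
2. State that post-randomisation values of the proposed mediators enter only a separate analysis, labelled exploratory mediation analysis. For example, it could relate the post-intervention mediator to the three-month outcome, with the no-confounding assumption stated. Its coefficients are not used for planning.

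The cost is analysis wording only. No measure, visit or data item changes.
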